### 6.2.3 Adverse event reporting

All AEs occurring during biomedical research projects involving human subjects are recorded in the CRF.

SAEs are reported and processed according to the applicable laws and regulatory requirements governing the conduct of biomedical research projects involving human subjects, i.e. all SAEs will be reported to the accredited METC that approved the protocol, according to the requirements of that METC.

Where appropriate, suspected unexpected serious adverse reactions (SUSARs) are reported and processed according to the applicable laws and regulatory requirements governing the conduct of biomedical research projects involving human subjects.

SAEs and SUSARs are additionally recorded on the SAE Form (**Appendix 3**) enclosed with the protocol. In case a pregnancy occurs it will be recorded on the pregnancy form (**Appendix 3**).

The filling-in of the SAE Form is detailed in the “Guidelines for completing the SAE Form” (**Appendix 4**) enclosed with the protocol.

The handling, processing and reporting of SAEs and SUSARs are described in detail in the study protocol and graphically presented in a flow-chart, enclosed with the study protocol (**Appendix 5**).

For SUSARs, study supplementation will be unblinded prior to reporting the case to the IRB/IEC and (if required) to the Health Authorities.

During or at the end of each study, an SAE reconciliation between data entered in the study database and the data entered in the pharmacovigilance database has to be performed if a pharmacovigilance database has been used. All discrepancies found during the reconciliation are documented in an SAE reconciliation report and corresponding queries are sent to the investigators for clarification.

### 6.2.4 Follow-up of adverse events

All adverse events will be followed until they have abated, or until a stable situation has been reached. Depending on the event, follow up may require additional tests or medical procedures as indicated, and/or referral to the general physician or a medical specialist.

# 7. STATISTICAL ANALYSIS

## 7.1 Descriptive statistics

Data will be presented as minimum, maximum, mean and standard deviation. Non-normally distributed parameters will be presented as minimum, maximum and medians.

## 7.2 Univariate analysis

For statistical analyses, the differences in effect of the placebo capsules and experimental capsules will be determined by comparing the changes between absolute concentrations as measured after the 4-week experimental period and the 4-week placebo period by using a paired T-test. Period and carry-over effects will be analyzed as described [21]. ANCOVA will be performed if baseline values are statistically different between the groups. If available, values of days 25 and 28 will be averaged to reduce within-subject variability.

Postprandial effects will be compared by using ANOVA with time, diet and subject number as factors. In all cases, a P-value <0.05 is considered to be statistically significant.

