# SUMMARY

**Rationale**: A substantial residual cardiovascular risk is still present, despite successful efforts to lower atherogenic serum low-density lipoprotein cholesterol (LDL-C) concentrations. An additive strategy may be raising high-density lipoprotein (HDL) concentrations, and in particular those of its major protein constituent apolipoprotein A-I (apoA-I). Based on cell and animal studies, resveratrol may be a promising candidate in this respect. Effects of this dietary component on apoA-I has however never been evaluated in a placebo controlled human intervention study.

**Objective**: To evaluate the effects of resveratrol on apoA-I concentrations in subjects with low serum HDL-cholesterol (HDL-C) concentrations at baseline. Minor objectives are to study the effects of resveratrol on (1) endothelial function and arterial stiffness as measured by flow mediated vasodilatation (FMD) and pulse wave velocity (PWV) during the fasting and postprandial phase (2) endothelial function of the retinal vasculature (3) lipid and glucose metabolism during the fasting and postprandial phase, and (4) biomarkers for low-grade systemic inflammation (interleukin-6 (IL-6), C-reactive protein (CRP)) and endothelial function (monocyte chemotactic protein-1 (MCP-1), sE-selectin, soluble intercellular adhesion molecule 1 (sICAM-1), and soluble vascular cell adhesion molecule-1 (sVCAM-1)).

**Study design**: A randomized, double-blind, placebo controlled cross-over design. The total study duration will be 12 weeks, consisting of a 4 weeks experimental period, a 4 weeks wash-out and a 4 weeks control period.

**Study population**: Fifty overweight and obese men and women, aged 45-70 years, with low HDL-C concentrations (men <1.0 mmol/L and women <1.3 mmol/L).

**Intervention**: During the experimental period, subjects will receive daily one capsule at lunch and one capsule at dinner, each providing 75 mg resveratrol. During the control period, subjects will receive daily two placebo capsules, each containing 58 mg cellulose.

**Main study parameters/endpoints**: Measurements will be performed at the start and end of each 4-week intervention period. Effects of resveratrol supplementation will be calculated as the absolute differences between values obtained at the end of each period. The primary endpoint is the change in serum apoA-I concentrations.

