**Primary research question:**

What is the effect of resveratrol supplementation on serum apoA-I concentrations in men and women with low HDL-C concentrations?

*Major null hypothesis, H_0_:*

As compared with control capsules, a daily intake of two capsules each containing 75 mg resveratrol for 4 weeks does not change serum apoA-I concentrations in subjects with low HDL-C concentrations.

*Major alternate hypothesis, H_a_:*

As compared with control capsules, a daily intake of two capsules each containing 75 mg resveratrol for 4 weeks does change serum apoA-I concentrations in subjects with low HDL-C concentrations.

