## 3.4 Sample size calculation

The statistical power to detect a difference of at least 50 mg/L in serum apo A-I concentrations between the experimental and control period is over 80%, when 45 subjects are included at P=0.05. For the calculations, a within-subject variability of 120 mg/L in serum apo A-I concentrations is used. As the expected drop-out rate is 10%, a total of fifty men and women will be recruited.

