### 5.2.5 Clinical Chemistry

Samples from the start and end of each experimental period (see table 4) will be analyzed at the Department of Clinical Chemistry and the Department of Haematology of the University Hospital Maastricht, according to routine procedures.

- Blood chemistry: phosphorus, sodium, potassium, chloride, calcium, creatinine, blood urea nitrogen (BUN), protein, albumin, gammaGT, aspartate-aminotransferase (AST), alanine-aminotransferase (ALT), alkaline phosphatase (ALP), bilirubin
- Haematology: White cell count, red cell count, platelet count, hemoglobin, hematocrit, mean cell volume, and mean cell hemoglobin concentration, red cell distribution
- Blood coagulation: Prothrombin time (PT) and aPT

Table 3: Time points at which blood samples will be drawn and metabolic risk markers will be measured

| **Day** | **Screening**  **(2 visits)** | **Days 0 and 56** | **Days 25 and 81** | **Days 28 and 84** | | | | | | | | |
| --- | --- | --- | --- | --- | --- | --- | --- | --- | --- | --- | --- | --- |
| **Timepoint (T=)** |  |  |  | **0** | **15** | **30** | **45** | **60** | **90** | **120** | **180** | **240** |
| Serum |  |  |  |  |  |  |  |  |  |  |  |  |
| ApoA1 |  | X | X | X |  |  |  |  |  |  |  |  |
| ApoB |  | X | X | X |  |  |  |  |  |  |  |  |
| Total cholesterol | X | X | X | X |  |  |  |  |  |  |  |  |
| LDL-C | X | X | X | X |  |  |  |  |  |  |  |  |
| HDL-C | X | X | X | X |  |  |  |  |  |  |  |  |
| Insulin |  | X | X | X | X | X | X | X | X | X |  | X |
| Triglycerides |  | X | X | X |  |  |  | X |  | X | X | X |
| hsCRP |  | X | X | X |  |  |  |  |  |  |  |  |
| EDTA |  |  |  |  |  |  |  |  |  |  |  |  |
| IL-6 |  | X | X | X |  |  |  | X |  | X |  | X |
| sICAM-1 |  | X | X | X |  |  |  | X |  | X |  | X |
| VCAM-1 |  | X | X | X |  |  |  | X |  | X |  | X |
| MCP-1 |  | X | X | X |  |  |  | X |  | X |  | X |
| sE-Selectin |  | X | X | X |  |  |  | X |  | X |  | X |
| Haematology and Clinical Chemistry |  | X |  | X |  |  |  |  |  |  |  |  |
| Resveratrol |  | X | X | X |  |  |  |  |  |  |  |  |
| Heparin |  |  |  |  |  |  |  |  |  |  |  |  |
| Metabolomics |  | X |  | X |  |  |  |  |  |  |  | X |
| NaFl |  |  |  |  |  |  |  |  |  |  |  |  |
| Glucose | X | X | X | X | X | X | X | X | X | X |  | X |

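### A baseline significance test decides whether the primary apoA-I comparison is baseline-adjusted; one model should be fixed in advance

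*Protocol*

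**What the plan says.** Section 7.2 compares absolute concentrations after the "4-week experimental period and the 4-week placebo period by using a paired T-test". The Summary agrees that the effect rests on end-of-period values: "Effects of resveratrol supplementation will be calculated as the absolute differences between values obtained at the end of each period". Where both are available, the day 25 and day 28 values are averaged.

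Baselines are nevertheless collected. The Summary states: "Measurements will be performed at the start and end of each 4-week intervention period". The sampling table in section 5.2.5, headed "Time points at which blood samples will be drawn and metabolic risk markers will be measured", lists apoA-I at days 0 and 56.

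The only route by which these baselines enter the treatment comparison is the conditional sentence in 7.2: "ANCOVA will be performed if baseline values are statistically different between the groups". The only significance level on offer is the general one: "In all cases, a P-value <0.05 is considered to be statistically significant". No unconditional baseline-adjusted analysis is stated. Section 7.2 does not say what the groups are in a design where every subject takes both products, or which baseline would be the covariate.

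**The concern.** A baseline test asks whether chance has produced an imbalance. Whether to adjust depends on a different matter: how well baseline predicts outcome within the comparison being made. In a randomised trial the first question carries almost no information about the second.

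Two consequences follow. The form of the primary analysis is settled by a feature of the data rather than in advance. And if the period baselines do carry information, it is discarded in nearly every realisation of the trial.

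The word *groups* makes this worse, because it has two readings:
- **Sequence groups at day 0.** The test looks at between-subject differences that the paired comparison already removes.
- **Treatments across days 0 and 56.** Half of the second-period baselines follow resveratrol, so carry-over can set off the switch to ANCOVA.

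**Working it through.** **Inputs from the protocol.** Section 3.4 gives a target difference ("detect a difference of at least 50 mg/L in serum apo A-I concentrations"), 45 evaluable subjects and a within-subject variability of 120 mg/L. The level is 0.05, taken as two-sided because the alternative hypothesis is that resveratrol "does change serum apoA-I concentrations in subjects with low HDL-C concentrations".

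**Assumptions.** 120 mg/L is read as the SD of the paired difference; section 3.4 does not say which SD it is. r is the correlation between a subject's baseline difference and end-of-period difference (resveratrol minus placebo). The protocol gives no value, so r = 0 to 0.5 is shown.

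**Step 1: the plan's own figure.** 50/(120/√45) = 50/17.89 = 2.795, and Φ(2.795 − 1.960) = Φ(0.835) = 79.8%. With the noncentral t, power is 78.0%. The stated figure of over 80% is reproduced to within 2 points on this reading.

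**Step 2: how often ANCOVA is run.** Without carry-over the mean baseline difference is zero in expectation, so the trigger fires with probability 0.05. Simulation gave 4.9% to 5.1%. ANCOVA is not run in about 95% of trials.

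**Step 3: what adjustment would change.** Residual variance is multiplied by 1 − r²: no reduction at r=0, 4% at r=0.2, 9% at r=0.3 and 25% at r=0.5. Simulated power for 50 mg/L with n=45:

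| r | Conditional rule | Always adjusted | Difference (points) |
|---|---|---|---|
| 0 | 78.2% | 77.5% | −0.7 |
| 0.2 | 78.0% | 78.6% | +0.6 |
| 0.3 | 77.8% | 80.6% | +2.8 |
| 0.5 | 78.7% | 87.5% | +8.8 |

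Type I error of the conditional rule was about 5.0% at r=0, 4.8% at r=0.3 and 4.4% at r=0.5. Always adjusting held 5.0% to 5.1%. Both statements are for no carry-over.

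**Step 4: which r is plausible.** Pairing has already removed stable between-subject differences. Let s be the correlation of a baseline with its own period's end value and x the correlation for every cross-period pair. Then r = (s − x)/(1 − x). If all four values are equally correlated, s = x and r = 0. With s = 0.85 and x = 0.80, r = 0.05/0.20 = 0.25.

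Days 0, 28, 56 and 84 are equally spaced. Under AR(1) decay with 28-day correlation φ, the covariance of the two differences is proportional to φ − φ³ − φ + φ = φ(1 − φ²), and each variance to 2(1 − φ²). So r = φ/2, which is below 0.5, and r = 0.4 needs φ = 0.8. A single-sample baseline set against a two-day mean lowers r further.

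**Step 5: carry-over, on the treatment reading of *groups*.** Suppose carry-over shifts the day 56 baseline by 0.25 or 0.5 SD of the baseline difference in the subjects who took resveratrol first, and has gone by day 84. The mean baseline difference then moves by about 0.12 or 0.24 SD. The trigger fires in about 12% or 34% of trials. Always adjusting is also affected: its type I error rises to about 6–7% at r=0.3 and 7–13% at r=0.5. The unadjusted comparison does not use day 56 and is untouched in this scenario.

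**The case against.** The strongest defence is that the paired default is already efficient and valid, so little turns on the rule. Much of this stands. With r at or below about 0.25, which equal correlation or AR(1) decay with sampling noise would give, the stake runs from about 1 point lost by adjusting to 1 or 2 points gained. A reader might infer that precision is lost in about 95% of trials. The protocol does not support that: it gives no r, and at r=0 there is nothing to lose. What fails in about 95% of trials is the use of the baselines.

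A reader might also infer that the rule inflates false positives. Without carry-over it does the opposite, slightly.

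Third, 7.2 says ANCOVA is performed, not that it replaces the t-test, and section 4.1.2 keeps the code sealed until the analyses are complete. Blinding does limit choosing by result. But if both analyses are run, 7.2 does not say which is primary, so the objection does not remove the problem.

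Fourth, defining the groups and the covariate is detail an analysis plan could supply. That is fair, and the missing definitions are not the point. The point is the trigger that the protocol does fix. A four-week wash-out and a separate carry-over analysis are planned, which makes the carry-over route less likely but does not exclude it.

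Finally, it is tempting to conclude that day 0 and day 56 must always be covariates. Step 5 shows why that does not follow.

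**Conclusion.** The point holds as a design fault of modest and uncertain size. Whatever r is, the adjustment of the primary comparison should not hang on a baseline significance test. That test is positive about 5% of the time by chance and does not measure prognostic value.

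The cost in power, relative to always adjusting, runs from a saving of about 1 point at r=0 to a loss of about 9 points at r=0.5. The upper end is unlikely given the pairing and the equally spaced measurement days. Type I error is about 5.0% down to 4.4% without carry-over.

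These figures assume 45 evaluable subjects, 120 mg/L as the SD of the paired difference, a 0.05 threshold for the baseline test, and r between 0 and 0.5. The carry-over figures rest on assumed shifts; the protocol gives no evidence that carry-over of that size occurs.

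**What to change.** Delete the conditional sentence from section 7.2 and name one primary model before unblinding:

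- Outcome: end-of-period apoA-I, the mean of the day 25 and day 28 values in period 1 and of days 81 and 84 in period 2.
- Effects: treatment, period and subject.
- No baseline significance test.
- A statement, made in advance, of whether the period baselines (day 0 and day 56) enter as covariates. If they do, include them in every case and report the model without them as a sensitivity analysis, because carry-over into day 56 would bias the adjusted estimate.

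The cost is a short rewrite of 7.2 and no new data. If the baselines are included, it also costs one degree of freedom, and about 1 point of power should they prove uninformative.

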## 4.2 Postprandial test

At the end of each intervention period (days 28 and 84), subjects will participate in a postprandial test. On the day preceding the test day, subjects will be asked to avoid high fat foods, alcohol, caffeine and taking part in any strenuous activity / exercise. On the morning of the test - after a 12 hr overnight fast (from 8 PM) - subjects are allowed to drink a glass of water in the morning. After arrival, subjects will be weighed and have to rest for 15 minutes in the supine position. Then, the first ECG, FMD and PWV measurements will be performed. After these first measurements, a venous cannula will be inserted and a fasting blood sample (t=0, 16.5 mL) will be collected. Subjects are then requested to consume, within 10 minutes, two muffins and 300 mL low-fat milk (see Tables 2 and 3). Subsequent blood samples are collected via the cannula at 15, 30, 45, 60, 90, 120 and 240 minutes (each 16.5 mL), as indicated in figure 1. After the last blood sample is taken, the cannula will be removed, a second FMD and PWV measurement is started. During the 4-hour period, subjects are allowed to drink water. This protocol will be followed during both postprandial test days (days 28 and 84).

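### Fitted with the three factors listed, the postprandial ANOVA tests diet against a pooled residual instead of subject-by-diet, so its nominal 5% level does not hold

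*Protocol*

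**What the plan says.** The whole analysis of the postprandial data is one sentence in Protocol section 7.2: "Postprandial effects will be compared by using ANOVA with time, diet and subject number as factors". It is judged by the general rule "In all cases, a P-value <0.05 is considered to be statistically significant". The sentence names no interaction, random effect, error stratum or covariance structure.

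Section 4.2 describes one test day at the end of each period: "This protocol will be followed during both postprandial test days (days 28 and 84". After the fasting sample, "Subsequent blood samples are collected via the cannula at 15, 30, 45, 60, 90, 120 and 240 minutes". Table 3 in section 5.2.5 shows which marker is measured when. FMD and PWV are measured before the meal and 4 hours after it (sections 5.2.2 and 5.2.3).

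For the comparison of end-of-period concentrations, section 7.2 instead uses a paired t-test, with the subject as the unit.

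**The concern.** Capsule type changes only between a subject's two test days. The samples taken within one day share that day's level, so they are not independent replicates of the treatment. The subject factor removes a subject's overall level. It does not remove the shift between that subject's two days, eight weeks apart. In a model with time, diet and subject only, that shift is spread over a residual with hundreds of degrees of freedom, and the standard error of the diet effect no longer reflects how often treatment was replicated.

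At stake are the postprandial parts of secondary questions 1 (FMD, PWV) and 3 (lipid and glucose metabolism), and the postprandial inflammation and endothelial markers in section 5.2.1. An ordinary difference between two days could be declared an effect of resveratrol. Under other variance patterns, a real effect could be missed.

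**Working it through.** **Inputs from the protocol**
- Subjects: n = 45, from section 3.4 ("is over 80%, when 45 subjects are included at P=0.05").
- Test days per subject: 2, one per treatment.
- Times per test day (m), counting t = 0, from Table 3 of section 5.2.5: insulin and glucose 8 (row "Insulin | | X | X | X | X | X | X | X | X | X | | X"); triglycerides 5 (row "Triglycerides | | X | X | X | | | | X | | X | X | X"); IL-6, sICAM-1, VCAM-1, MCP-1 and sE-selectin 4. FMD and PWV: 2. The fifth triglyceride time is 180 minutes, which is in Table 3 but not in the section 4.2 list; without it, triglycerides have m = 4.
- Level: 0.05.

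**Inputs assumed, because the protocol gives none**
- ρ: share of the residual variance (set to 1) that is test-day variation; the rest, 1 − ρ, is within-day error. Range 0.2 to 0.8.
- τ: subject-by-time variance (differently shaped curves), relative to that residual variance. Values 0, 1 and 2.

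**The plan's own figure.** The only one on this point is the nominal 5%. It is reproduced when ρ = 0 and τ = 0: the two mean squares below are then equal.

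**Degrees of freedom**
- Pooled residual: 2nm − 1 − (n − 1) − 1 − (m − 1) = 2nm − n − m. This gives 180 − 47 = 133 (m = 2), 360 − 49 = 311 (m = 4), 450 − 50 = 400 (m = 5) and 720 − 53 = 667 (m = 8).
- Subject-by-diet: n − 1 = 44.

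**Expected mean squares with no diet effect**
- Diet, and likewise subject-by-diet: A = (1 − ρ) + mρ.
- Pooled residual: B = (1 − ρ) + [44mρ + 2 × 44(m − 1)τ] / df.
- With k = A/B, the actual error rate is about 2[1 − Φ(1.96/√k)].

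**Worked cases**
- m = 4, ρ = 0.8, τ = 0: A = 0.2 + 3.2 = 3.4; B = 0.2 + 3.2 × 44/311 = 0.653; k = 5.2; 1.96/√5.2 = 0.86; rate 39%.
- m = 8, ρ = 0.8, τ = 0: A = 6.6; B = 0.2 + 6.4 × 44/667 = 0.622; k = 10.6; rate 55%.
- m = 2, ρ = 0.2, τ = 2: A = 1.2; B = 0.8 + (17.6 + 176)/133 = 2.256; k = 0.53; rate 0.7%.

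**Error rate of the diet test by the formula, for ρ = 0.2 / 0.5 / 0.8**

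| Times per day | τ = 0 | τ = 1 | τ = 2 |
| --- | --- | --- | --- |
| 2 (FMD, PWV) | 8 / 15 / 21% | 2 / 5 / 8% | 1 / 2 / 4% |
| 4 (soluble markers) | 14 / 27 / 39% | 4 / 11 / 19% | 1 / 5 / 10% |
| 5 (triglycerides) | 16 / 32 / 44% | 5 / 15 / 24% | 2 / 7 / 14% |
| 8 (glucose, insulin) | 23 / 42 / 55% | 9 / 23 / 34% | 4 / 13 / 23% |

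Simulation of the same model agrees within about two percentage points. For τ = 0 it gives 8-22%, 14-41%, 16-46% and 22-55% for 2, 4, 5 and 8 times.

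**Break-even.** Setting A = B gives mρ(df − 44) = 88(m − 1)τ. Since df − 44 = 89(m − 1), this means τ = (89/88)mρ. The pooled test holds 5% only if subject-by-time variance happens to be about m times the test-day variance, or if both are zero. Below that point it rejects too often, above it too rarely.

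**Proper error term.** Tested against subject-by-diet on 1 and 44 df, which is the paired t-test on each subject's test-day means, diet was rejected in about 4-6% of simulated trials in every setting.

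**The case against.** **The pooled error is inferred.** The protocol does not say that one residual is used. The same sentence could be shorthand for a within-subject ANOVA that tests diet against subject-by-diet, which holds its level, and an analysis plan not shown here may say so. This stands as a limit on the claim. It does not remove it: the sentence lists its factors, and an analyst who fits exactly those gets the wrong error term.

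**The size depends on assumptions.** A reader might infer that this trial has a false-positive rate of up to 55%, or that the test must be anti-conservative. The documents support neither. The high figures need a large test-day share and identical curve shapes in all subjects. With a small test-day share (0.05 to 0.1) and no subject-by-time variance, simulated rates for 4 to 8 times are 7-14%. With clearly different curves the rate can fall below 5%.

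**The contrast is open.** If the postprandial effect were meant as diet-by-time, the inflation would not apply. However, no interaction is listed. In the same single-error model with no subject-by-time variance, such a test would reject only 0-4%, so it would be miscalibrated too.

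**The outcomes are secondary.** This stands. A reader might infer that the trial's main conclusion is threatened. It is not: fasting apoA-I is compared by a paired t-test. Secondary question 4 does not itself mention the postprandial phase; its markers come in through section 5.2.1.

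**Conclusion.** The concern holds in a limited form. Read as listed, the section 7.2 model lacks the error term that matches how treatment was replicated, and its diet test keeps 5% only if both variance components are absent or happen to balance. The departure is about 8-55% over the assumed test-day shares of 0.2 to 0.8 when curves are parallel across subjects, and about 1-34% when subject-by-time variance is one to two times the residual variance. Neither size nor direction is fixed by the documents, so these are ranges under stated assumptions and not an error rate for this trial. Severity is moderate.

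**What to change.** State the error term in section 7.2. Either of these is enough:

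1. A mixed model with fixed time and diet, random subject and random subject-by-test-day effects, and a random subject-by-time effect where it can be estimated. Diet is then tested against between-day variation.
2. One prespecified summary per subject and test day, such as the time-weighted mean over 0-4 h, with treatments compared within subject on 44 df at 45 subjects. This uses the same between-day error and matches the paired approach already used in 7.2.

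Whether to subtract the fasting value (incremental area, or 4 h minus fasting for FMD and PWV) is a separate choice of contrast. It should be made on its own merits and is not needed to repair the error term. If diet-by-time is of interest, the text should say so and name its error term as well.

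The cost is wording only: no new data or visits. Confidence intervals for the postprandial outcomes may be wider. If the correct model was already intended, nothing changes except that the text says so.
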